### Statistical analyses

The primary analysis will be undertaken on an intention-to-treat basis, and two-sided tests will be applied at a 5% alpha level. Following assessment of normality, treatment effects will be analysed using a generalized estimating equations (GEE) approach that allows for analysis of longitudinal data while accounting for the correlation among the repeated observations for each subject [45]. GEE analyses will also be used to examine dose-effect relationships and to explore possible confounding effects of site or relevant subgroups such as age or ASD subtype.

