#### Description of music therapy

The duration of music therapy sessions will be 30 minutes. Therapists conducting the music therapy sessions will be trained music therapists (master's level or equivalent) with clinical experience of working with children with ASD.

The music therapy approach applied in this study is based on the ideas and principles of improvisational music therapy [26,27], findings from previous music therapy research [13,15-17,28], and developmental psychology [29]. The music played or sung by the therapist is generally attuned to the child's (musical or other) behaviour and expression and includes various improvisational techniques to engage the child and establish contact with the child. To this end, "musical" features of the child's expression (pulse, rhythmic, dynamic or melodic patterns, timbre etc.) may be mirrored, reinforced, or complemented, thus allowing for moments of synchronisation between child and therapist and giving the child's expressions a pragmatic meaning within the context. To allow elicitation of specific social communicative behaviours, the therapist may also gently provoke the child e.g. by violating expectations or jointly developed patterns. While engaging in joint musical activities within a shared history of interaction, the child is offered opportunities to develop and enhance skills such as affect sharing, joint attention, imitation, reciprocity, and turn-taking, all of which are associated with later development in language and social competency [30,31].

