### Power calculation and sample size

#### Estimate of effect size

A Cochrane review on music therapy for ASD found effect sizes (standardised mean differences) of d = 0.50 and 0.36 for gestural and verbal communicative skills, respectively [7]. However, these figures were derived from small studies with low precision and using unpublished scales [7]. A more precise estimate using the ADOS scale may be derived from the PACT trial [6] where an effect of d = 0.24 was found. That study was more similar in design to the present study but used a different behavioural intervention. In summary, an effect size in the small (d = 0.20) to medium (d = 0.50) range may be expected [35], corresponding to a 1 to 2.5 points difference on the ADOS scale that typically has SD = 5 [6]. An effect size in this range would be clinically meaningful as the ADOS scale measures the core symptoms of ASD which are difficult to influence with any treatment.

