#### Parameters for sample size calculation

The two music therapy arms (high- and low-intensity) will be taken together for the primary analysis to answer the question if music therapy in general is superior to standard care. Half of all participants will be assigned to music therapy. In light of the uncertainty around the true effect size and the difficulty of recruiting large samples, a group sequential design (GSD, [36]) will ultimately ensure 80% power (two-sided alpha 0.05) even for a small effect, while avoiding excessively large sample size if there is in fact a medium effect. We used the common Lan-DeMets alpha spending function and a Pocock boundary to make early stopping likely. Calculations and simulations were made for up to four equally spaced looks, using East 5.4 software by Cytel Inc., 2010.

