#### Results

Table 1 shows that if there is a medium effect of music therapy, power at the first interim look (usable N = 235) will be 93%. Power will also be acceptable (76%) if the effect is slightly smaller than medium. If there is only a small effect size, power can still be retained by recruiting more participants. An independent data monitoring committee will perform the interim look. We will aim to randomise N = 300 participants (150 to standard care and 75 to each type of music therapy) to account for possible drop-outs and clustering within sites [37]. However, the actual interim look may be taken at a different sample size, depending on recruitment progress and funding.

**Table 1 T1:** Sample size and power under different scenarios

Raw difference on the ADOS scale (SD = 5)	Standardised effect size (Cohen's d)	Power at first interim look^1^	Test power over all 4 interim looks^2^
2.5	0.5 (medium effect)	93%	100%

2	0.4	76%	100%

1.5	0.3	47%	99%

1	0.2 (small effect)	20%	80%

Note. Based on 10000 simulations for each scenario. ^1^Usable N = 235 (300 randomised). ^2^Maximum usable N = 939.

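### The sample size allows for clustering within sites, but the stated primary GEE handles only within-child correlation, so the nominal error rate is not assured in either direction

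*Protocol article*

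**What the plan says.** Three parts of the protocol article bear on this.

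- **Power calculation and sample size (Results).** The first look is planned at 235 usable children, with 300 to be randomised "to account for possible drop-outs and clustering within sites". No ICC, cluster size or drop-out rate is given, and the two reasons share one allowance.
- **Study design.** Children are randomised individually, 1:1:2, in blocks of 4 or 8 from a list specific to each site. For the primary comparison, "The two music therapy arms (high- and low-intensity) will be taken together for the primary analysis", so the contrast is effectively 1:1.
- **Statistical analyses.** Treatment effects are estimated by GEE, "accounting for the correlation among the repeated observations for each subject". Site is mentioned only afterwards, as something whose possible confounding will be explored alongside subgroups.

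On delivery, the Description of music therapy says "Therapists conducting the music therapy sessions will be trained music therapists (master's level or equivalent)" and that they have experience with autistic children. The number of therapists and the number of children per therapist are not stated. Parent counselling, which all three arms receive, is given by a music therapist, a clinical psychologist or both.

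**The concern.** The sample size section treats children as correlated with one another. The analysis section names a model for correlated measurements within one child. A robust variance clustered on the child does not pick up correlation between children, so the dependence allowed for in the sample size has no counterpart in the stated analysis.

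Two sources of dependence matter, and they act differently:

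- **Site.** Every site contributes to all arms through its own blocked list, so a shared site effect largely cancels in the treatment contrast. A model without site leaves that variation in the residual and tends to overstate the standard error. Site makes the standard error too small only if the treatment effect itself differs between sites.
- **Therapist.** Music therapy is given one-to-one by a therapist who may treat several children. If therapists differ, outcomes in the music therapy arms are correlated within therapist, and this does not cancel against standard care. Ignoring it makes the standard error too small.

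At stake are the true size of the primary test, at the first look and overall, and the width of the confidence interval.

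**Working it through.** **1. Reproduce Table 1.** The inputs come from the power section: two-sided alpha 0.05, a Lan-DeMets spending function with a Pocock boundary, four equally spaced looks, SD 5 and pooled arms of 235/2 = 117.5.

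- Alpha spent at a quarter of the information: 0.05 × ln(1 + (e − 1) × 0.25) = 0.01787, so z = 2.368.
- First-look power = Φ(d√235/2 − 2.368). For d = 0.5, 0.4, 0.3 and 0.2 this gives 92.8%, 75.7%, 47.3% and 20.2%. The table has 93%, 76%, 47% and 20%.
- Power over four looks at N = 939, by simulation with computed boundaries: 100%, 100%, 99.0% and 80.1%. The table has 100%, 100%, 99% and 80%.

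Table 1 therefore assumes independent children. Any allowance for clustering lies only in the step from 235 to 300, a factor of 300/235 = 1.277.

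**2. What that step leaves for clustering.** Drop-out rates are assumed.

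- 10%: 270/235 = 1.15
- 15%: 255/235 = 1.09
- 20%: 240/235 = 1.02

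**3. Therapist correlation ignored by the analysis.** Let ρ be the therapist ICC and m the number of music therapy children per therapist, both assumed. Take standard care as uncorrelated.

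- Design effect in the music therapy arms: DE = 1 + (m − 1)ρ.
- Variance ratio, true to naive, for the difference: R = (1 + DE)/2.
- True size = 2[1 − Φ(z/√R)], with z = 1.96 for a nominal 5% test and z = 2.368 for the first look.

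| ρ | m | DE | R | SE ratio | Size, nominal 5% | Size, nominal 1.8% |
|---|---|---|---|---|---|---|
| 0 | any | 1.00 | 1.00 | 1.00 | 5.0% | 1.8% |
| 0.01 | 5 | 1.04 | 1.02 | 1.01 | 5.2% | 1.9% |
| 0.02 | 10 | 1.18 | 1.09 | 1.04 | 6.1% | 2.3% |
| 0.05 | 10 | 1.45 | 1.225 | 1.11 | 7.7% | 3.2% |
| 0.10 | 10 | 1.90 | 1.45 | 1.20 | 10.4% | 4.9% |
| 0.10 | 15 | 2.40 | 1.70 | 1.30 | 13.3% | 6.9% |

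**4. Offset from the omitted site stratum.** If a share ρₛ of the outcome variance lies between sites and cancels in the contrast, the ratio becomes about R − ρₛ. Take ρ = 0.02 and m = 10:

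- ρₛ = 0.05: 1.09 − 0.05 = 1.04, true size about 5.5%.
- ρₛ = 0.10: 1.09 − 0.10 = 0.99, true size about 4.9%.

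The direction of the net error thus depends on quantities the article does not give.

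**5. Power once the allowance is used.** With 15% drop-out, 255 children remain. At d = 0.4 and m = 10, first-look power is Φ(0.4√(255/R)/2 − 2.368):

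- ρ = 0.02: effective N = 255/1.09 = 234, power about 76%.
- ρ = 0.05: 255/1.225 = 208, about 70%.
- ρ = 0.10: 255/1.45 = 176, about 61%.

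The table states 76%.

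**The case against.** The strongest reply is that this is a journal article. Its analysis section describes the GEE in one sentence and does not say that only within-child correlation will be modelled. Covariates and variance estimators are commonly left to the full protocol or SAP. That would dispose of a complaint about silence. It does not remove the mismatch: the article names the model, names the correlation it handles and gives site an exploratory role, after sizing the trial for clustering within sites and stratifying randomisation by site.

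A reader might infer more, and four stronger readings are not supported:

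- **That standard errors are too small.** This needs a positive therapist ICC. At ICC 0.01 with five children per therapist the effect is negligible, and the omitted site stratum pushes the other way.
- **That the sample size was inflated for therapists and the analysis then ignored them.** The allowance is for sites. Therapists presumably work within sites, so the phrase may have been meant to cover them, but the article does not say so. Nor is it shown that site was the wrong unit to name.
- **That standard-care children share no provider.** Counselling may be given by music therapists in every arm, so some clustering in standard care is possible.
- **That Table 1 overstates power.** Applying a design effect to 235 counts clustering twice, since the step from 300 already includes an allowance for it.

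Therapist variation may also be limited by the treatment guide, video-based fidelity rating and supervision. Against that, the guide is to be applied flexibly and relies on clinical expertise. The documents do not settle how large the ICC is.

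**Conclusion.** The point holds as a mismatch between the sample size section and the stated primary analysis, with an uncertain effect on the error rate. Neither the site stratum used in randomisation nor therapist-level correlation enters the treatment-effect model as described. For the assumed range of ICC and caseload, the true size of a nominal 5% test runs from about 5.2% to 13.3% before any offset from site. With a small therapist ICC and a moderate site ICC it can fall just below 5%. These sizes rest on assumed values, on a partially nested structure with no clustering in standard care, and on a normal approximation. The planned power is not shown to be wrong: with 15% drop-out it is preserved at ICC 0.02 and ten children per therapist, and falls short at 0.05 and above.

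**What to change.** **In Statistical analyses:**

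- Include site as a fixed-effect covariate in the primary model, matching the stratified randomisation.
- Record a therapist ID for every child in the music therapy arms.
- Allow for therapist-level correlation in those arms, for example by a partially nested term or by a variance clustered on therapist with a small-sample correction. If it is not part of the primary model, make it a pre-specified sensitivity analysis.

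**In Power calculation and sample size:** give the drop-out and design-effect parts of the step from 235 to 300 separately, with the assumed ICC and cluster size.

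**Cost:** one data field and a few sentences, somewhat wider intervals where therapists differ, and possibly slightly lower stated power. Putting site in the model costs essentially nothing. A therapist ID that is not recorded during the trial may be hard to recover later.

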### Ethical issues

The study protocol was approved by the Faculty of Humanities' Human Research Ethics Board (HREB) at Aalborg University, Denmark. Freely given, written informed consent will be obtained from participant's parents/guardians prior to study enrolment in accordance with regulatory requirements. Random allocation of participants to study groups is considered reasonable as no adverse effects are expected in any of the conditions. Inconveniences caused by the necessity to attend three weekly sessions of music therapy for the families assigned to this study group are considered tolerable in view of the anticipated benefit for the child receiving therapy.

## Discussion

High clinical applicability of this RCT's findings is to be achieved through therapy conditions that are close to clinical practice in terms of broad eligibility criteria (verbal and non-verbal children, all types of ASD), treatment duration (several months), and therapy techniques (improvisational music therapy conducted by experienced therapists in a typical setting).

The study's limitations are also its strengths: The absence of outcomes proximal to music therapy [15,17]; the heterogeneity of standard care as a control condition; and the heterogeneity of the population [46] may be seen as limitations, but are features that will improve feasibility and that are in line with pragmatic trials of effectiveness whose focus is to help users choose between options [47].

Conclusions that will emerge from this study are expected to contribute to the evidence base of treatment options for children with ASD. The results of the trial will provide evidence on the effectiveness of music therapy as a treatment for ASD and will also provide information on the relevance of session frequency for therapy outcome. Furthermore, findings gained through the application of a treatment guide within this study may help to further specify music therapy treatment guidelines for this population and to enrich future training and education of music therapists and other health care professionals working in the field of ASD.

Findings of this study will also be relevant for other fields where music therapy is applied, such as adult mental health [10,25], and for basic research into the musical qualities of early mother-infant communication providing a rationale for music therapy [18,29]. Music therapy in general is an intervention that focuses on developing social and emotional abilities, and ASD is a case in point because impairments in these abilities are central for ASD.
